## Abstract

**Background:**

There is some evidence that people with intellectual disabilities who live in the community are exposed to the same risks of alcohol use as the rest of the population. Various interventions have been evaluated in the general population to tackle hazardous or harmful drinking and alcohol dependence, but the literature evaluating interventions is very limited regarding intellectual disabilities. The National Institute for Health and Clinical Excellence recommends that brief and extended brief interventions be used to help young persons and adults who have screened as positive for hazardous and harmful drinking. The objective of this trial is to investigate the feasibility of adapting and delivering an extended brief intervention (EBI) to persons with mild/moderate intellectual disability who live in the community and whose level of drinking is harmful or hazardous.

**Methods/Design:**

The study has three stages, which include the adaptation of the Extended Brief Intervention (EBI) for people with intellectual disability, a single blind, randomised controlled trial of an individual Extended Brief Intervention to test the feasibility of the intervention, and a qualitative study that will assess the perceived acceptability and usefulness of the intervention. Fifty participants in total will be recruited from community intellectual disability services and social care or third sector organisations. The main outcome is a reduction in alcohol consumption measured by the Alcohol Use Disorders Identification Test.

**Discussion:**

Alcohol misuse is a relatively under-researched mental health problem in people with intellectual disabilities. Therefore, the study addresses both diagnostic issues and the delivery of a simple first stage intervention, which is available to the population of average intelligence and young persons in particular. The findings from the study will guide the preparation of a large-scale study to test whether this treatment is clinically and cost-effective in this population.

**Trial registration:**

ISRCTN58783633 (19 December 2013).

## Background

Alcohol is the most commonly used substance worldwide and contributes substantially to mortality, psychiatric and physical health morbidity and causes increased disease burden [1,2]. Despite the sparse literature regarding substance misuse in people with intellectual disabilities (characterised by an Intelligence Quotient (IQ) less than 70, developmental delay and adaptive deficits), there is increasing interest in studying such problems in this population. This is because most now live in the community and are more likely to be exposed to substances [3,4]. United Kingdom and United States population-based studies indicate that the prevalence of substance misuse in people with intellectual disabilities ranges from 0.5% and 2.5%, respectively, to as high as 25% for any substance in clinic samples [4-6]. Approximately 5% of the youth in drug and alcohol services have a degree of intellectual disability [1]. The most common substance that people with intellectual disabilities tend to use is alcohol, followed by cannabis and cocaine [2]. Aetiological factors that have been postulated to contribute to substance misuse in people with mild to moderate intellectual disabilities include hyperactivity, lack of assertiveness, low self-esteem, susceptibility to peer pressure, desire for social acceptance, social isolation, early onset of drinking and lack of example setting in childhood [1]. Substances may also be taken as a maladaptive way of relieving stress or developing relationships within local communities [7,8]. Those most at risk are young males with a mild intellectual disability or borderline intelligence who live independently and are less likely to engage in activities and/or to experience mental health problems [1].

Brief and extended brief interventions have been evaluated in the general population to tackle hazardous or harmful drinking and alcohol dependence. Despite the heterogeneity observed in the studies, a meta-analysis showed that participants generally have lower alcohol consumption at one year (mean difference: -38 grams/week, 95% CI: -54 to -23 and mean difference = -28, 95% CI: -62 to 6 grams/week, for brief and extended brief interventions, respectively) [9]. The same meta-analysis reports that loss to follow-up ranges from 10% to 70% but only three studies reported such rates. However, the literature evaluating any interventions targeted at people with intellectual disabilities is uncommon. This is partly due to the general lack of evidence based interventions in this field, but also to the belief that interventions that are suitable for typically functioning adolescents and adults are also suitable for those with mild-moderate intellectual disabilities without need for adaptation. This seems counterintuitive as people with intellectual disabilities have cognitive deficits that impair their ability to learn or generalise new learning, and therefore may require interventions to last longer, to include maintenance sessions, and to be supported to seek help and attend appointments. It is often reported that staff delivering interventions to the general population may not be skilled to provide such treatment to people with intellectual disabilities [8].

A variety of approaches have been tried to help people with mild to moderate intellectual disabilities and substance misuse, including education about the risks associated with substance misuse, behavioural modification, and the use of adapted materials from Alcoholics Anonymous or similar organisations, mostly delivered in group settings [10-16]. As a whole, these studies suggest that the capacity of people with intellectual disabilities to learn new information is enhanced by providing additional cues and using techniques such as modelling, videotaped vignettes and role-playing [15]. Often, sessions are augmented with coping skills lessons and assertiveness training [17]. However, the studies conducted to date are small, run in specialist single centre settings and are uncontrolled.

Nevertheless, two studies merit further attention; one is a study of three sessions of group motivational interviewing over two weeks conducted with seven offenders with intellectual disabilities in a medium secure unit [18]. The authors found that the participants showed increased determination to reduce drinking at the end of the treatment. The second study [15], was a 10-week evaluation of assertiveness training and modelling to educate about substance misuse and to help the participants (N = 84) to respond appropriately when offered substances in their social network. The authors found that knowledge of the risks associated with use of illicit substances increased at the end of the intervention, and this was maintained at six- months follow-up. The methodological limitations of the studies include the uncontrolled design, the small sample size, insufficient details of reporting, inclusion of several types of substances in the educational materials and the delivery in a specific environment that is different from community living.

The National Institute for Health and Clinical Excellence (NICE) (PH24; [19]) recommends that brief and extended brief interventions are used to help young persons and adults who have screened positive for hazardous and harmful drinking. The interventions recommended are based on motivational interviewing/enhancement techniques, and are delivered by trained professionals. Their aim is to reduce alcohol intake, reduce risk-taking behaviour and even to consider abstinence. The sessions are short at 30 minutes and follow-up is offered. At all times, individuals who are referred for treatment have their capacity to consent to it assessed and, where further treatment is indicated, referrals to secondary specialist services should be made.

We chose to evaluate the Extended Brief Intervention (EBI) in the current study because it is a widely used and evaluated treatment in the literature for hazardous and harmful drinking. It is a low-intensity intervention and can be delivered by trained professionals in the public and voluntary sector.

### Aims and objectives

The key research question is: Can we design a large scale, randomised controlled trial (RCT) that will answer whether EBI is more effective than usual care in helping adults with mild to moderate intellectual disability to reduce their alcohol intake?

The feasibility trial will compare the use of EBI with treatment as usual in the participating areas and will enable us do the following:measure the number of eligible participants, including paid and family carers, willingness of clinicians to recruit participants, recruitment rate, loss to follow-up, adherence to the intervention, and standard deviation of the primary outcome measures. This will ultimately inform the sample-size calculation for a multicentre clinical trial.determine the acceptability of randomisation to service users through its effect on dropout rates and qualitative interviews.determine, through response rates to questionnaires, the appropriateness and the acceptability of the outcome measures to service users and their carers in order to explore the suitability of our chosen secondary outcome measures, that is, days abstinent, service use and health-related quality of life.estimate the time needed to collect and analyse dataexplore the utility of the health-related quality of life questionnaire in allowing the estimation of quality-adjusted life years in the sample.

We will also conduct qualitative interviews with service users, their carers, and service providers, to assess the acceptability of the treatment and to explore their experience of the treatment including any barriers and/or facilitators to taking part in the study. Findings from these interviews will enable us to refine the EBI.

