### Stage 2-Feasibility study

#### Design

This will be a single blind, randomised controlled trial of individual EBI delivered as an adjunct to usual care for alcohol use disorders (AUD). Fifty participants, randomised to either the intervention arm or usual care, will be assessed at baseline, two months and three months. Research assistants carrying out assessments will be blind to the trial arm to which the participants are allocated.

Finally, qualitative interviews will be carried out at three months (see stage 3 below).

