#### Randomisation and masking

Randomisation will be conducted by contacting an external researcher once the potential participant has consented to take part in the study and baseline data have been collected (class A method of randomisation). The research team statistician will generate the randomisation list. Any breach in blinding/unmasking, a common problem with single blind trials, will be monitored to ensure that the research assistants are not aware, as far as possible, to which group the individual was allocated. The researchers will make a note of which group he/she believes the participant has been allocated to for all participants and this will be compared to the actual allocations at the end of the study. The database management will be supervised by the PRIMENT Clinical Trials Unit and the study statistician GB.

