#### Statistical analysis

The analysis of the data will be mainly in terms of descriptive statistics and point and interval estimations with the express aim to inform a future multicentre trial. No hypothesis testing will be performed. We will compare drop-out rates in the intervention and treatment-as-usual arm, and means, medians, interquartile ranges, counts and proportions to estimate effect size will be calculated. Regression models allowing for participant clustering will be considered to examine the association between the primary outcome and sociodemographic and clinical predictors. The results will be presented with 95% confidence intervals.

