### Stage 3-Qualitative study

In order to assess the perceived acceptability and usefulness of the intervention, 50% of service user and carer dyads allocated to the EBI arm of the trial, will be interviewed at end of treatment (that is, 12 weeks). The interviews will be completed by the two service users who are supported to contribute to the study reference group (part of the trial management group), with support from the research assistants. Both service users and the research assistants will be trained in how to collect qualitative data and conduct the interviews. We will include participants who may have dropped out of treatment, if at all possible, in order to ascertain their perceptions of the intervention and their reasons for dropping out. Interviews will be audiotaped and analysed using content analysis and/ or thematic analysis [33,34].

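### The two sources named for judging whether randomisation is acceptable give only weak, indirect evidence: drop-out is compared only between randomised arms, and the interviews sample only the EBI arm

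*Protocol article*

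**What the plan says.** Under Aims and objectives, one listed aim is to "determine the acceptability of randomisation to service users through its effect on dropout rates and qualitative interviews". That fixes two sources of evidence: drop-out and interviews.

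**Drop-out.** The Design section says "Fifty participants, randomised to either the intervention arm or usual care, will be assessed at baseline, two months and three months". No unrandomised or preference group is described. Under Randomisation and masking, allocation happens "once the potential participant has consented to take part in the study and baseline data have been collected". The Statistical analysis section gives one drop-out analysis: "We will compare drop-out rates in the intervention and treatment-as-usual arm".

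**Interviews.** Stage 3 defines the sample: "50% of service user and carer dyads allocated to the EBI arm of the trial, will be interviewed at end of treatment". Its stated purpose is "In order to assess the perceived acceptability and usefulness of the intervention". On people who left treatment it adds: "We will include participants who may have dropped out of treatment, if at all possible". They are to be asked how they saw the intervention and why they left. Aims and objectives describes the interviews, which there also cover service providers, as meant "to assess the acceptability of the treatment and to explore their experience of the treatment including any barriers and/or facilitators to taking part".

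The recruitment rate and the number of eligible people are also to be measured, but under a separate aim. The article does not link them to the acceptability of randomisation.

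**The concern.** The aim speaks of an effect of randomisation on drop-out, yet everyone in the stated drop-out comparison has been randomised. What is compared is one allocation with the other. People who object to randomisation in principle are likely to say no at approach, before they can be counted as drop-outs.

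The interviews could fill that gap, but the sample as fixed hears only from people who agreed to take part and were then offered the new intervention. Two groups with an obvious reason to object are outside it: those allocated to usual care, which the article itself says usually brings little specific support, and those who declined.

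The key research question is whether a large randomised trial can be designed, and willingness to be randomised is one of the unknowns the study lists for itself. If the plan is followed exactly, a statement that randomisation is acceptable would rest on evidence about something else, or on a selected group.

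**Working it through.** The article gives no figure to reproduce. The check is who enters each source, what the arm contrast can show, and how precise it would be.

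**1. Who is covered by each named source**

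| Group | Arm comparison of drop-out | Service-user and carer interviews |
|---|---|---|
| EBI, stayed in treatment | Yes | Yes, from a 50% sample |
| EBI, left treatment | Yes, if this counts as drop-out | If possible |
| Usual care | Yes | No |
| Consented, left before allocation | No | No |
| Declined at approach | No | No |

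**2. What the arm contrast shows.** As a simple additive illustration, let *b* be background drop-out common to both arms, *r*(E) and *r*(U) the drop-out due to having been randomised and to the result in each arm, and *s* the net effect of the EBI sessions (burden raises it, appeal lowers it).

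- EBI drop-out = *b* + *r*(E) + *s*
- Usual-care drop-out = *b* + *r*(U)
- Difference = [*r*(E) − *r*(U)] + *s*

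If randomisation is disliked equally in both arms, *r* cancels and the difference equals *s*, however large the dislike. If the dislike is unequal, it cannot be separated from *s*. Refusals before allocation appear in neither term.

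**3. Number of interviews.** Total sample 50 (Design). The allocation ratio is not stated, so 1:1 is assumed, giving 25 per arm. Half of 25 is 12.5, so 12 or 13 EBI dyads, 0 from usual care and 0 decliners.

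**4. Precision of the drop-out comparison.** With 25 per arm and a common drop-out proportion *p*, the 95% half-width for the difference is 1.96 × √(2*p*(1 − *p*)/25). The range for *p* is the 10% to 70% loss to follow-up that the Background cites from a meta-analysis in the general population. It serves only as an illustration.

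| *p* | Half-width (percentage points) |
|---|---|
| 10% | 16.6 |
| 20% | 22.2 |
| 30% | 25.4 |
| 50% | 27.7 |
| 70% | 25.4 |

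At 30%: 1.96 × √(2 × 0.3 × 0.7/25) = 1.96 × √0.0168 = 0.254.

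**5. Purpose of the interviews.** The aim relies on them for the acceptability of *randomisation*. Both descriptions of the interviews give their purpose as the acceptability of the *intervention or treatment*. The only wording that could reach randomisation is the reference to barriers and facilitators, and Stage 3 still limits the service users and carers who are asked to the EBI arm.

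**The case against.** The strongest reply is that a reader might infer the aim cannot be met at all, and the text does not support that. Higher drop-out in usual care would be indirect evidence of dissatisfaction with allocation. EBI interviewees can be asked how they felt about being randomised, and the barriers-and-facilitators wording leaves room for it. Withdrawals between consent and allocation could be counted. The recruitment rate partly reflects refusal. In a descriptive study without hypothesis tests, the aim may loosely mean: do people leave once allocated? All of this stands, and it is why the evidence is called weak and indirect, not absent.

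Second, topic guides and reason-for-refusal fields are commonly left to a full protocol, and the recruitment flow diagram is not shown. That is fair, so their absence is no part of the point. The point rests on what the article does fix: the interview sample, its purpose and the drop-out contrast.

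Third, a reader might infer that the answer is bound to lean towards acceptable. That is not established. EBI asks for five weekly sessions and a later one, with a carer in attendance, and the Discussion expects some people to be unwilling to commit to treatment. Some may object more to being allocated to EBI than to usual care.

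Fourth, wide intervals are expected in a feasibility study, and an interval of ±25 points can still exclude very large differences. That also stands. Imprecision is secondary to the mismatch between the aim and its evidence.

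**Conclusion.** The concern holds in a limited form. The aim on acceptability of randomisation and the evidence named for it do not match, even if the plan is carried out exactly as written. Drop-out by arm confounds reaction to allocation with the effect of the EBI sessions and leaves out refusals before allocation. The service-user and carer interviews leave out usual care and decliners. The result may be biased, probably but not certainly towards acceptable.

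The figures depend on assumptions: 1:1 allocation throughout, and 30% drop-out for the half-width of about 25 points. The range of about 17 to 28 points covers drop-out from 10% to 70%. The mismatch itself depends on none of these. It affects one feasibility aim, not the primary outcome or the sample size, and is worth correcting because the repair is cheap.

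**What to change.** 1. **Measure refusal directly.** Among people approached, record who refuses and why, with objection to randomisation as one of the listed reasons. Report the proportion refusing for that reason, with a 95% confidence interval, as the main measure for this aim. State that full eligibility will be unknown for some refusers, because the Participants section places the IQ assessment after consent unless an earlier result exists.
2. **Hear from both arms.** Take a few of the planned interviews from usual-care dyads and ask interviewees in both arms about being allocated by chance. For example, 4 of the 12 or 13 would leave 8 or 9 in EBI. Amend the Stage 3 purpose to include randomisation.
3. **Relabel the drop-out comparison.** Report it with its interval as differential attrition, and describe it as only indirect evidence on randomisation.

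The cost is one extra log field, a wording change and slightly fewer EBI interviews to inform refinement of the intervention. If that loss matters, the usual-care interviews can be added to the planned number instead, at the price of a few more interviews. Decliners would still not be interviewed, so the refusal log would be the only information on them. The article reports recruitment still open at submission, so the log could start at least for people not yet approached.

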## Methods/Design

The study corresponds to Phase 2 of the Medical Research Council (MRC) complex interventions guidelines, which guides the development of an intervention [20]. Therefore, the study has three stages that will be discussed below.

### Stage 1-Adaptation of the intervention

We will review the literature on EBI, and we will consult with service users and professionals about the number of sessions to be delivered and the materials to be used in each session. This is particularly important as people with intellectual disabilities have substantial cognitive deficits that require a longer duration of treatment, a mixture of materials, and the opportunity to test skills learnt over time [21]. So while the adapted intervention will include the existing treatment, such as a detailed assessment of drinking behaviour and the development of coping plans, it will be also include strategies to make engaging with the intervention easier, such as repetition of information and longer sessions.

The treatment manual will be tested with three service users (see Inclusion criteria below) in terms of acceptability and clarity, and the intervention will be refined accordingly. A similar approach has been used in a previous study [22]. The data from these individuals will not be included in the final analysis of the results.

### Stage 2-Feasibility study

#### Design

This will be a single blind, randomised controlled trial of individual EBI delivered as an adjunct to usual care for alcohol use disorders (AUD). Fifty participants, randomised to either the intervention arm or usual care, will be assessed at baseline, two months and three months. Research assistants carrying out assessments will be blind to the trial arm to which the participants are allocated.

Finally, qualitative interviews will be carried out at three months (see stage 3 below).

#### Setting

The study will be conducted within the Community Intellectual Disabilities Teams and social care services in three participating areas in England, UK, including urban and inner city locations. These teams offer specialist mental health, social care support and health services to adults with intellectual disability, as well as residential and supported living accommodation.

